## Abstract

**Introduction:**

The period directly after primary treatment for breast or prostate cancer is a time when patients feel unprepared about how to manage life and address unexpected health challenges. Supportive care should focus on identifying symptoms and concerns and involving survivors in their self‐care. Interventions using a blended model encompassing remote and in-person components may inform how supportive care can be organised. This protocol describes two pilot randomised controlled trials with the aim to investigate the acceptability, feasibility and potential effects of a 6 month digital and nurse-led support intervention in primary care for patients with breast or prostate cancer during the first year after primary treatment.

**Methods and analysis:**

Two cluster randomised pilot trials including patients with breast or prostate cancer during the first year after ending primary treatment will run from 2023 in primary care centres in Region Stockholm. The trials will have an estimated sample size of 20 patients in each arm. The intervention groups receive a digital and nurse-led support intervention in combination with standard care, and the control groups receive standard care alone. To assess acceptability and feasibility, the participants in the intervention groups and the study nurses will be interviewed. Furthermore, digitally logged data and field notes by study-specific nurses will be analysed. Data collection for the potential effects of the intervention is conducted through self-reported standardised and validated questionnaires at baseline, and at 3, 6, 12, 18 and 24 months. Data entry and analyses will be blinded to the researchers. Qualitative data will be analysed with content analysis, quantitative data will be evaluated by comparing changes within and between groups.

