### Study design

The study design is underpinned by the Medical Research Council (MRC) framework for complex interventions.^32^ These studies have cluster randomised controlled pilot trial design including patients with breast and prostate cancer, respectively, during the first year after ending primary treatment. The two pilot RCTs will be performed in PCCs in Region Stockholm. The studies have two parallel arms: the intervention plus standard care (intervention group) and standard care alone (control group). The intervention involves an entire PCC, and cluster randomisation is used to avoid the spill-over effect.^33^ To achieve representativeness for the cluster randomisation, the Care Need Index (CNI) for calculating economic compensation to the PCC is used.^34^ CNI measures healthcare needs for the distribution of primary care resources to populations with the biggest need. A high CNI equals low socioeconomic status, and a low CNI equals high socioeconomic status. Ten PCCs in the region were considered sufficient as a basis for our sampling. Five pairs of PCC were matched to the CNI and the size of the PCC regarding a number of allocated patients. Subsequently, a randomisation through sealed envelopes allocated the PCC to either intervention or control in each pair.

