### Participants

#### Enrolment

The recruitment and participant enrolment were started in October 2023 and is expected to continue until January 2026. Patients diagnosed with breast or prostate cancer and who have ended primary treatment are identified through the database at the Stockholm Centre for Health Data on healthcare consumption by combining PCC individual identification codes and relevant ICD-10 codes. Criteria for inclusion are completed primary treatment with curative intent for breast or prostate cancer within the past 6 months, >18 years and able to speak and understand Swedish. The criterion for exclusion is cognitive impairment. The plan is that the intervention can be given during the first year after primary treatment and that the intervention period of 6 months falls within the frame of the first year. Eligible patients in the intervention PCC and the control PCC are consecutively recruited by an invitation letter prepared by the researchers and posted from the PCC. Patients who agree to participate return an informed consent form directly to the researchers (online supplemental material). A reminder is sent within 2 weeks to those who have not been heard from. The patients are then contacted by the researcher who estimates the possibility of inclusion with regard to the inclusion criteria.

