#### Potential effect outcomes

To evaluate the potential effects of the intervention and obtain estimates for a future full-scale trial, outcomes are collected through self-reported standardised and validated questionnaires at baseline, and at 3, 6, 12, 18 and 24 months after intervention has started. HRQoL and symptom distress are assessed by the European Organisation for the Research and Treatment of Cancer Quality of Life Questionnaire EORTC-QLC-C30^43^ including disease-specific modules QLQ-PR25,^44^ QLQ- BR45^45^ and EQ-5d-5L^46^; the Patient Activation Measure for knowledge, skills, beliefs and confidence of managing health and healthcare^47^; the Sense of Coherence Scale-13, which measures overall coping ability^48^ and communicative and critical health literacy (5-items).^49^ The quantitative data will be triangulated with interview data from patients to explore perceptions regarding the effects of the intervention.

Medical data will be obtained from patients’ medical records. Demographic data (age, education, marital/civil status, having children at home, employment status, sickness absence) and comorbidity are self-reported. For the data measurement plan, see table 1.

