### Analyses methods

Descriptive statistics will be used to analyse logged data from the use of the app, and descriptive qualitative analyses will be used for interview data. For the comparison of the potential effect measures between the groups, inferential and comparative statistical analyses appropriate for data level and distribution will be used, and mixed methods analysis will be applied to integrate quantitative and qualitative data.^52^

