### Potential benefits and limitations

There are good reasons to believe that the routine collection of ePRO facilitates person-centred care where the patient is a participatory member of the team. Early identification of symptoms may guide symptom management and self-care ability, prevent more illness and lead to a faster return to daily activities and a better quality of life. Integrating this way of taking care of patients in need of support after cancer treatment in primary care could facilitate scheduling healthcare visits targeting the patients in need of surveillance.

This study protocol will inform the development of a future definitive larger trial. As a pilot RCT, in the protocol we have described primarily aims to answer questions of acceptability and feasibility. For this reason, we have not powered the study to formally test any hypothesis of efficacy or adequately understand sources of individual differences in intervention efficacy. The external validity is limited, although we propose that results from a larger trial may be transferable to other care settings for patients with other chronic diseases.

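### The abstract counts within-arm change towards the evaluation although only the between-arm contrast can show a potential effect; that contrast is best estimated with adjustment for baseline

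*Protocol article*

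**What the plan says.** Two places in the protocol article describe the quantitative analysis, and they differ.

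- Abstract, Methods and analysis: "quantitative data will be evaluated by comparing changes within and between groups". Within-group change is listed beside the between-group contrast, with nothing to mark it as descriptive.
- Analyses methods: "For the comparison of the potential effect measures between the groups, inferential and comparative statistical analyses appropriate for data level and distribution will be used". Only the between-group comparison appears. Neither within-group tests nor change scores are mentioned, and the model is left open.

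The purpose of the effect outcomes is given under Potential effect outcomes: "To evaluate the potential effects of the intervention and obtain estimates for a future full-scale trial". The questionnaires are completed "at baseline, and at 3, 6, 12, 18 and 24 months after intervention has started", so every scale has a baseline value. Enrolment requires patients to have "completed primary treatment with curative intent for breast or prostate cancer within the past 6 months". Study design provides a parallel arm that receives standard care alone. Potential benefits and limitations adds that "we have not powered the study to formally test any hypothesis of efficacy".

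**The concern.** Patients are recruited soon after a demanding treatment and followed for two years. Symptoms and quality of life may well shift over that time with standard care alone. A before-and-after comparison inside the intervention arm adds that shift to anything the intervention does, and no analysis of that arm alone can take the two apart. The control arm exists for this reason. A plan that lists within-group change as a means of evaluation, without calling it descriptive, invites readers to take an improvement in the intervention arm as a sign of benefit.

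The second part is about precision. The pilots are meant to supply estimates for a full-scale trial, from about 18 evaluable patients per arm. If the between-group comparison of changes is made on follow-up minus baseline, the interval will be wider than the same data allow. What is at stake is the quality of the planning estimate; the pilots make no efficacy claim.

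**Working it through.** **Inputs from the protocol article.** Sample size asks for 18 evaluable patients in the intervention arm and allows 10% dropout: 18 / (1 − 0.10) = 20 per arm, which reproduces the stated figure. The calculations below use n = 18 per arm.

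**Assumed inputs.** The document gives no correlation r between baseline and follow-up and no size for recovery under standard care. Ranges are used: r from 0.3 to 0.8, recovery from 0.2 to 0.5 SD. The SD is taken as equal at both times, and clustering is ignored.

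**Step 1: within-arm test when the intervention does nothing.** Both arms recover by g SD. The change has SD √(2(1 − r)), so the paired t-test in one arm has noncentrality g√n / √(2(1 − r)). For g = 0.5 and r = 0.5 this is 0.5 × √18 / 1 = 2.12, and the chance of a significant improvement (two-sided 5%) is 0.516. A simulation of 20,000 trials gave 0.515. The last column is the chance that the intervention arm is significant and the control arm is not, taking the arms as independent.

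| Recovery in both arms | r | Intervention arm significantly improved | Intervention arm significant, control arm not |
|---|---|---|---|
| 0.2 SD | 0.5 | 0.123 | 0.108 |
| 0.2 SD | 0.7 | 0.177 | 0.146 |
| 0.3 SD | 0.5 | 0.224 | 0.174 |
| 0.3 SD | 0.7 | 0.341 | 0.225 |
| 0.5 SD | 0.5 | 0.516 | 0.250 |
| 0.5 SD | 0.7 | 0.733 | 0.196 |

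**Step 2: between-arm test in the same setting.** In the simulation (g = 0.5, r = 0.5, n = 18) the two-sided rejection rate was 5.1% for change scores and 5.1% for ANCOVA. Recovery common to both arms cancels.

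**Step 3: precision of the between-arm difference, in SD units.**

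- Change scores: SE = √((2/n) × 2(1 − r)).
- Baseline-adjusted (ANCOVA): SE = √((2/n) × (1 − r²)).
- Variance ratio, ANCOVA to change score: (1 − r²) / (2(1 − r)) = (1 + r)/2.

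| r | SE, change scores | SE, ANCOVA | Variance ratio | Patients per arm for change scores to match ANCOVA with 18 |
|---|---|---|---|---|
| 0.3 | 0.394 | 0.318 | 0.65 | 27.7 |
| 0.5 | 0.333 | 0.289 | 0.75 | 24.0 |
| 0.7 | 0.258 | 0.238 | 0.85 | 21.2 |
| 0.8 | 0.211 | 0.200 | 0.90 | 20.0 |

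The last column is 18 divided by the variance ratio. The gain shrinks as r rises. In interval width, √0.65 = 0.81 and √0.85 = 0.92, so adjustment narrows the interval by about 19% at r = 0.3 and about 8% at r = 0.7.

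**The case against.** The strongest reply is that the abstract is a summary and Analyses methods governs. That section speaks only of comparison between groups, nothing says that a within-arm change will be read as an effect, and the same abstract clause keeps the between-group contrast. This largely stands, and it limits the point to the within-group half of one clause. It does not remove the point, because the abstract is the only place that names specific contrasts and it names one that the main text does not. Nor does having a control arm protect a reader who compares two within-arm tests: the last column of the first table shows how often only the intervention arm would reach significance.

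A second reply is that changes need not mean raw change scores. The wording fits a repeated-measures model as well, and an analysis plan that is not shown may settle how baseline enters. This also stands. Baseline adjustment is a recommendation prompted by the wording, not the correction of an analysis that the document has fixed.

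Several stronger readings are tempting, but the document does not support them:

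- *Recovery will pass for an effect in the between-group comparison.* It cancels there when it is common to both arms.
- *Change scores waste the baseline.* They use it and are unbiased under randomisation; they only use it less efficiently.
- *Regression to the mean drives the within-arm change.* The Enrolment section recruits consecutively and sets no symptom or quality-of-life threshold, so patients are not selected for extreme scores.
- *Inferential analysis contradicts the statement on power.* That statement disclaims power. It does not rule out inference, which includes interval estimation, and the sample size itself rests on a confidence-interval approach.
- *Chance baseline imbalance arises from having ten centres.* With 20 per arm the baseline difference has SD √(2/20) = 0.32 without clustering. With an assumed intracluster correlation of 0.05 and four patients per centre it is √(2 × 1.15/20) = 0.34. Nearly all of it comes from the number of patients.
- *A within-arm improvement would wrongly trigger the definitive trial.* No progression rule based on effect is stated. The strengths and limitations list ties the question of a future trial to acceptability and feasibility.

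**Conclusion.** The point holds in a limited form, as a free improvement. The abstract and Analyses methods differ on whether within-group change is part of the evaluation. In patients enrolled this soon after treatment, such change should not count as evidence of a potential effect. With no effect at all, a within-arm test would show improvement in 12% to 73% of trials over the assumed range (recovery 0.2 to 0.5 SD, r 0.5 to 0.7, n = 18), against about 5% for the between-arm test.

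The between-arm comparison is valid on change scores or with adjustment. If change scores are used, adjustment would reduce the variance to 0.65 to 0.85 of theirs for r of 0.3 to 0.7. These figures rest on assumed correlations and recovery sizes, equal SDs and no clustering. The direction does not depend on the chosen values: within-arm change is confounded with any recovery, and (1 + r)/2 is below 1 whenever r is below 1. The consequence is a misleading or less precise planning estimate, not a false efficacy conclusion.

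**What to change.** 1. Bring the abstract into line with Analyses methods, so that potential effects are assessed by comparison between groups.
2. Define the effect estimate as the between-arm difference at each follow-up visit, adjusted for the patient's baseline value of the same scale, by ANCOVA or by a mixed model over visits, allowing for primary care centre. Report it with a confidence interval.
3. Present within-arm changes descriptively, without tests, and say that they are not read as effects.

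The cost is wording alone. The baseline questionnaire is already part of the schedule, no interim analysis is planned, and analysis waits until all patients have finished the intervention. Sample size, visits and conduct of the trials stay as they are.

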**Ethics and dissemination:**

This project was reviewed and approved by the Swedish Ethical Review Authority. Study results will be published in peer-reviewed journals and presented at scientific and professional meetings.

**Trial registration numbers:**

ClinicalTrials.gov, NCT06471452 and NCT05100121.

Strengths and limitations of this studyThe two pilot studies are cluster randomised and have a prospective, repeated measure design.The rigorous design is underpinned by the Medical Research Council framework for complex interventions and the use of patient interviews, clinical guidelines and literature reviews.The digital nurse-led intervention includes the use of an interactive app previously tested in randomised controlled trials with positive results.The acceptability and feasibility measures in the pilot trial will offer insight into whether a future definitive trial can be done and into the recruitment process.The pilot study sample may be too limited in terms of size and geographical sites to be representative and to capture a potential effect of the intervention.

## Introduction

### Background

 Breast and prostate cancer account for more than half of all cancer incidences and are the most common form of cancer in women and men in Sweden.^1^ Advances in the treatment of breast or prostate cancer have improved rates of survival and quality of life, but many patients have long-lasting symptoms and concerns in the aftermath of treatment.^2^,^5^ Primary treatment for breast cancer is commonly surgical excision followed by radiotherapy and/or chemotherapy depending on the type of tumour.^6^ In addition, endocrine therapy is frequently prescribed over a long period, up to 10 years, often rendering long-term side effects such as lack of energy, hot flashes, sleep difficulties and joint pains.^7^ Difficulties in handling side effects can lead to non-adherence to prescribed treatment and thereby render a greater risk of cancer recurrence.^8^ After primary treatment for prostate cancer—surgical excision or radiotherapy—most men need regular surveillance, and some are prescribed long-term adjuvant antiandrogens. All treatments for prostate cancer may have a long-term impact on the patients’ quality of life and sexual, urinary and bowel functions.^9 10^

Many patients in the first year after primary treatment for breast or prostate cancer have unmet informational, physical, psychological and emotional healthcare needs.^11 12^ The period directly after primary treatment has been recognised as a time when patients feel unprepared about how to manage life and must address unexpected challenges, not knowing what to do about it, or where to seek assistance.^13^ Lingering symptoms and concerns remain after treatment for prostate cancer, and timely information and support are considered important by patients.^14^ Patients with breast cancer describe how they try to manage by themselves, but express a wish for extended and more individually tailored support.^15^

Supportive care should focus on identifying symptoms and concerns and involving patients in their self‐care to improve long‐term health.^16^ In Europe, there is no formalised indication of how supportive care should be organised, and many survivors after ending primary treatment are expected to be seen in the primary care setting.^16^ In Sweden, the basic health and medical care for most common conditions and illnesses is generally referred to as primary care. There are guidelines from the European Society for Medical Oncology (ESMO) showing that patient-reported outcomes should be used in the clinic to include any aspect of a patient’s health status that comes directly from a patient.^17^ Symptom self-monitoring in the continuum of cancer care using electronic patient-reported outcomes (ePRO) is recommended by ESMO and should include questions for evidence-based symptoms, with the advantage of automated alerts to clinicians for worsening symptoms. Studies integrating ePRO to support patients in clinical practice with cancer during treatment have shown promising results such as decreased symptom burden and increased health-related quality of life (HRQoL)^18^,^20^ and survival^21^ in comparison to control groups. Studies also show high user engagement as well as feelings of security and satisfaction with easy access to caregivers.^22 23^ Research findings in a review article disclose a considerable variation in the features offered in the different symptom reporting systems.^20^ The review shows that over half of the systems had the facility for healthcare providers to monitor patient data over time, while fewer than half included the facility for patients to monitor and review their own data. Furthermore, less than half had general patient information about cancer treatment and side effects, and only one-third had automated patient advice on symptom management. Another recent review of digital health studies showed that positive outcomes were shown when the intervention targeted symptom reporting and self-care functions in combination, but only a few studies had also provided personal interaction.^24^ Optimal supportive care goes beyond just using ePRO. While ePRO plays an important role in the assessment of outcomes, it is essential that these outcomes are appropriately managed in clinical practice.^25^

Nurse-led interventions in cancer care, reported in an overview of reviews, comprised a combination of educational and psychosocial interventions.^26^ The review did not disclose if the studies were performed during or after treatment. The effectiveness of the interventions was inconsistent but significant when supporting patients’ coping, which included symptom education, problem‐solving therapy and coordinating and monitoring the treatment. Another review focusing on characteristics of care models for cancer survivorship describes that models using technology to enhance remote interaction between patients and healthcare providers improve the quality and effectiveness of care.^27^ Many of the care models used simple methods of communication such as websites, telephone calls and SMS messaging, and they position technology as a practical means to increase provider capacity and improve access to care. A minority of the described interventions used a blended model encompassing both remote and in-person components. The blended models were better suited for interventions detecting potential complications that may require clinical support. The duration of the interventions varied, and it was concluded in the review that, in studies of short duration, it was difficult to ascertain whether patients and providers had engaged with these models long enough to derive sustained outcomes. Studies reporting on nurse-led support interventions for patients with cancer, specifically in the context of primary care, are few. A pilot study to promote self-care for prostate cancer survivors showed that an educational nursing intervention was feasible and that the men gained some positive health outcomes.^28^ The intervention included an initial face-to-face appointment with follow-up visits as agreed. The nurse-led sessions were not based on ePRO, and there was an inconsistency in the follow-up visits, whereas less than one-third of the patients returned for a second or a third follow-up.

Supportive nursing interventions in cancer care have shown to be effective to varying degrees. The evidence is not conclusive, perhaps due to the complexity of nursing interventions with numerous components. The literature describes a variation of deliverance, and the shortcomings of such interventions and the number of studies conducted during the first year after primary treatment are unclear. Interventions involving ePRO are demonstrating rapid growth and have been shown to be helpful and effective for symptom management and the supportive care of patients with cancer. Intervention studies where ePRO and in-person support are simultaneously offered are still in their beginning stages. Also, in this field of research, reviews identify gaps in how to integrate ePRO for best clinical practice. The period directly after primary treatment is a time when patients feel unprepared and unsure where to seek care, whereas the primary care centres (PCCs) are often the given option. We seek to find out whether an ePRO intervention in combination with nurse-led support in the primary care setting is viable or in need of modifications ahead of a larger-scale evaluation of effectiveness. These parallel-running pilot RCTs are the first steps of preparation towards larger trials to deliver an intervention that includes important aspects as suggested in the literature.

